## Abstract

**Introduction:** Transgender women (assigned “male” at birth but who do not identify as male) are disproportionately impacted by HIV and experience unique barriers and facilitators to HIV care engagement. In formative work, we identified culturally specific and modifiable barriers to HIV treatment engagement among transgender women living with HIV (TWH), including prioritizing transition-related healthcare over HIV treatment, avoiding HIV care settings due to gender-related and HIV stigma, concerns about potential drug interactions with hormones, and inadequate social support. Grounded in the investigators' Models of Gender Affirmation and Health Care Empowerment, we developed the *Healthy Divas* intervention to optimize engagement in HIV care among TWH at risk for treatment failure and consequential morbidity, mortality, and onward transmission of HIV.

**Methods and Analysis:** We conducted a 2-arm randomized controlled trial (RCT) of the intervention's efficacy in Los Angeles and San Francisco to improve engagement in care among TWH (*N* = 278). The primary outcome was virologic control indicated by undetectable HIV-1 level (undetectability = < 20 copies/mL), at baseline and follow-up assessment for 12 months at 3-month intervals.

**Ethics and Dissemination:** This study was approved by University of California, San Francisco Institutional Review Board (15-17910) and Western Institutional Review Board (20181370). Participants provided informed consent before enrolment in the study. We are committed to collaboration with National Institutes of Health officials, other researchers, and health and social services communities for rapid dissemination of data and sharing of materials. The results will be published in peer-reviewed academic journals and scientific presentations. We will make our results available to researchers interested in transgender health to avoid unintentional duplication of research, as well as to others in health and social services communities, including HIV clinics, LGBT community-based organizations, and AIDS service organizations.

**Clinical Trial Registration:**
Clinicaltrials.gov, identifier NCT03081559.

## Introduction

### Background and Rationale

Evidence of the disproportionate rates of HIV infection, AIDS-related mortality, and uncontrolled viral load among transgender women has been rapidly increasing. Transgender women have 49 times higher odds of HIV infection compared to other groups, a disparity that exists across cultures and socioeconomic boundaries (1). Disparate prevalence of HIV is particularly pronounced for African American transgender women (2). In San Francisco, high HIV incidence and prevalence persist among African American transgender women, at 1.4 per 100 person-years and more than 30%, respectively (3). Compared to other populations in the city, viral suppression is lowest among transgender women living with HIV (TWH) (68%) (4). Further, lack of engagement in care and not being on antiretroviral therapy (ART) is high among TWH in San Francisco at 14.3 and 13%, respectively (5). Among African American TWH who had ever enrolled in HIV care in nearby Alameda County, more than one third had not received ART (6). Similarly, in Los Angeles, HIV prevalence among transgender women is high at 16.7% (7). Although transgender individuals make up only 0.1% of the city's population, 1.3% of all people living with HIV and 1.4% of recently diagnosed individuals are transgender (7). Among African American people living with HIV in Los Angeles, 26.5% are transgender (7) and among street- and venue-recruited transgender women, overall HIV prevalence ranges from 21.9–26.1% (8, 9). Transgender women are estimated to have the lowest proportion of viral suppression of any behavioral risk group (69%) (10).

Active engagement in clinical care and high levels of ART adherence are critical to allow people with HIV to live longer, healthier lives. Among persons diagnosed with HIV infection, 63% have successful virologic control as evidenced by suppressed viral load (11). Inconsistent engagement and retention in care (i.e., defined as at least two HIV care visits within 12 months with each visit 3 months apart) has been associated with death among HIV+ adults (12). TWH are less likely to be retained in HIV care and receive ART than other groups, (13, 14) and TWH on ART demonstrate worse ART adherence (15) and viral suppression (16) than non-transgender people on ART and report less confidence in their abilities to integrate treatment regimens into their daily lives (17). Further, like other populations, TWH not on ART or are not adherent to ART are at increased risk for elevated viral load, which increases the risk of emergence of drug-resistant virus and transmission of HIV to others. Among TWH, experiencing higher levels of social adversity is significantly associated with lower odds of viral suppression (18), with African American/Black TWH less likely to be retained in care and to reach viral suppression than Black non-transgender counterparts (19).

Addressing the culturally unique barriers to HIV care and adherence is vital to improving health outcomes among TWH (20). TWH face a complex array of psychosocial challenges that complicate their access and adherence to HIV care, such as limited access to and refraining from healthcare due to stigma and past negative experiences with providers, prioritization of gender-related healthcare, and concerns about adverse interactions between ART medications and hormone therapy. (21, 22) Social and economic marginalization due to transphobia (negative societal attitudes toward transgender persons) often result in poverty and unstable housing, familial alienation, limited formal education, limited social support, mental illness, trauma and victimization, substance use, and introduction to sex work often at an early age (23–29). These factors can result in late or no presentation to HIV medical care and poor health outcomes (30). Culturally responsive intervention efforts, in addition to gender affirming services and caring relationships with interventionists (31), may be most effective for improving care engagement and health outcomes among TWH at the individual level (32). Recent evidence from Los Angeles and San Francisco indicate that among transgender women of color living with HIV, the implementation of peer-delivered interventions positively impacts HIV care visit attendance, receipt of ART prescriptions, and retention in HIV care (33–36).

The non-HIV related medical concerns of transgender women (regardless of HIV status) differ from non-transgender persons. The desire for gender-affirming healthcare, such as hormone therapy, is a critical factor that is sometimes at odds with effective engagement in HIV medical care (37). Anecdotal reports from healthcare providers indicate that hormone treatment can be an incentive for TWH to seek and adhere to ART (38). In our formative work, TWH repeatedly reported misinformed fears that ART can limit the effect of hormones, a serious concern for this population. Finally, in our prior work, TWH have reported that HIV medical providers often do not have expertise in transgender health and that providers specializing in transgender health do not also specialize in HIV care. When transgender women were compared to other respondents, regardless of the current medication regimen, they were significantly less likely to report positive interactions with healthcare providers (17). Taken together, TWH may feel lost between multiple medical settings that are not integrated. Faced with this dilemma, many TWH have reported that they may priorities gender-affirming healthcare over HIV treatment (39).

This study is a randomized controlled trial (RCT) to intervene systematically on complex barriers to optimal engagement in HIV care specifically for TWH (see Figure 1 for Schedule of enrolment, intervention, and assessments / CONSORT Diagram). It is grounded in the investigators' Models of Health Care Empowerment (HCE) (40–42) and Gender Affirmation (GA) (43) (see Figure 2 for the *Healthy Divas* conceptual model integrating the Models of Gender Affirmation and Health Care Empowerment). We developed the *Healthy Divas* intervention to optimize engagement in HIV care for TWH at elevated risk for virologic failure and consequential morbidity, mortality, and transmission of HIV. We conducted a feasibility pilot test of the intervention with TWH using the same eligibility criteria as this RCT. We did not design the pilot to detect an effect size with which to power this RCT, as such efforts are problematic given the high likelihood of false negatives/positives inherent with small samples (44). Results from this RCT will have the potential to transform gender-affirming HIV healthcare for a population at dramatically elevated risk for disparately negative personal and public health outcomes.

**Figure 1 F1:**
[figure not shown]
Schedule of enrollment, intervention, and assessments / CONSORT Diagram.

**Figure 2 F2:**
[figure not shown]
*Healthy Divas* conceptual model integrating the Models of Gender Affirmation and Health Care Empowerment.

#### Choice of Comparators

For our control condition, we considered several alternatives and weighed several issues, including Safer and Hugo's guidance for identifying active intervention elements while controlling for potential confounding effects (45). When considering a time and attention matched control condition, we found that identifying an inert intervention that would not directly or indirectly tap into the constructs of gender affirmation and healthcare empowerment through discussions of topics of interest was a challenge. Such a control intervention may have had non-specific effects that threatened our power to detect effects of the *Healthy Divas* intervention. Therefore, we decided on a treatment as usual (TAU) control condition in which participants randomized to the control condition were offered the intervention content after their final assessment point. As part of this design, we used measures to assess and control for exposure to adherence counselling and support outside of the trial for TWH in both conditions (46). We also accounted for variability in the treatment as usual control condition by assessing standard care quality (SCQ), as described by de Bruin et al., and used the SCQ measure as a covariate in our analyses of intervention effects. (46, 47) Recognizing that an effect on outcomes using this design will provide useful but incomplete evidence for this intervention, we identified potential future steps to evaluate the effectiveness of this intervention in comparison to other approaches. Given the relative strengths and weaknesses of any choice of control condition, our design represents a critical next step in the development of the evidence base for a high-risk population with disparately poor HIV outcomes.

### Objectives

Building from our formative quantitative and qualitative interviews with patients and providers, focus groups, and piloting and refinement of the intervention, this RCT had the following aims:

Primary Aim 1: To evaluate odds of virologic control for TWH in response to the *Healthy Divas* intervention.

Hypothesis 1: TWH randomized to *Healthy Divas* will achieve or maintain higher odds of undetectable viral load than TWH assigned to a treatment as usual control condition.

Secondary Aim 2: To evaluate the efficacy of the intervention on HIV treatment engagement among TWH.

Secondary Hypothesis 2: TWH assigned to *Healthy Divas* will have higher engagement in HIV care (appointment attendance, ART uptake, adherence, and persistence) than the control group.

Secondary Aim 3: To explore the effect of the intervention on hypothesized mechanisms of action.

Secondary Hypothesis 3: TWH assigned to *Healthy Divas* will report more favorable scores on theory-based constructs of healthcare empowerment, gender affirmation, adherence self-efficacy, satisfaction with medical care, social support, HIV treatment information, and treatment beliefs and expectancies.

### Trial Design

This study was designed as an interventional 2-arm randomized controlled superiority clinical trial with two parallel groups and a 1:1 allocation to compare *Healthy Divas* to a TAU control condition. The *Healthy Divas* intervention is a combination of six individual sessions with a peer counsellor and a peer-led small group workshop with other TWH, and a provider with expertise in HIV primary care and transgender healthcare, all completed within 3 months. TWH (*N* = 278) were enrolled at two sites (117 in San Francisco; 161 in Los Angeles) who were confirmed to be living with HIV and showed evidence of suboptimal engagement in care, defined as meeting one or more of the following three indicators: (a) not on ART, (b) on ART but reporting non-adherence, (c) reporting no HIV care appointments in the prior 6 months. The primary outcome was virologic control, defined as undetectable viral load. Secondary exploratory outcomes were (a) within-subject improvement in scores on our engagement in HIV clinical care composite index, which includes ART uptake, ART adherence, and self-reported attendance at HIV primary care appointments; and (b) change in hypothesized mechanisms of action (e.g., healthcare empowerment, gender affirmation). The intervention began immediately following randomization and was completed prior to the 3-month follow-up assessment. Follow-up assessments, including viral load assays and surveys, occurred for 12 months post-randomization at 3-month intervals (see Figure 1 for the Schedule of enrolment, intervention, and assessments). Monthly check-in visits promoted contact between visits and allowed regular monitoring of HIV medical care.

## Methods

### Participants, Interventions, and Outcomes

#### Study Setting

This study was conducted in San Francisco and Los Angeles, California. An estimated more than 900 transgender women live in the city of San Francisco (46, 47), not including hundreds of transgender women in the East Bay region. Epidemiological data from Los Angeles County estimates that there are over 7,000 transgender women living in Los Angeles County (DHSP, 2012). All study activities occurred in community-based research locations separate from clinical care sites, minimizing confounding with clinic attendance. In San Francisco, our field site was located in the Tenderloin area and in Los Angeles our field site was located on the border between Hollywood and West Hollywood, areas with high HIV prevalence and community viral load burdens in San Francisco and Los Angeles, respectively. Both sites have working relationships with dozens of community-based agencies and clinics in the area and are centrally located near public transportation access.

#### Eligibility Criteria

Potential participants were considered eligible if they were ≥18 years; assigned male sex at birth but did not currently identify as male; English- or Spanish-speaking; HIV-positive confirmed via antibody testing; and reported suboptimal engagement in HIV care, as indicated by one or more of the following: (a) Not on ART; (b) If on ART, reporting less than perfect adherence on a validated adherence rating scale; or (c) Reporting no HIV primary care appointments in the prior 6 months.

Potential participants were considered ineligible if they exhibited evidence of severe cognitive impairment or active psychosis, as determined by the Project Director in consultation with the Principal Investigator (PI), a licensed clinical psychologist.

Individuals were not excluded if they were actively engaged in substance use. Substance use is prevalent in TWH, and exclusion based on active substance use would have resulted in a sample that does not represent the target population. Informed by our prior work (21), the intervention includes a focus on the role of substance use and alcohol in optimizing engagement in care. However, if an individual was intoxicated at the time of a visit, we rescheduled the session to preserve the integrity of the data collection and intervention delivery.

We considered only enrolling TWH with detectable viremia but opted for inclusion based on indicators of poor engagement instead. This approach allowed the intervention to prevent potential treatment failure in TWH whose patterns of engagement in care put them at risk of poor outcomes. We contended that this was likely to be a more cost-effective long-term approach, as preventing virologic failure may have greater individual and public health benefit than waiting to intervene until treatment failure. It was also more exportable to community settings, thus enhancing external validity; if the intervention demonstrates efficacy, agencies will be able to adopt it with easier screening procedures than if eligibility had been based on clinical parameters such as viral load. From a methodological perspective, this decision allowed more statistical power, as the primary outcome could fluctuate in both directions for the two randomized groups, thereby increasing internal validity. We anticipated that 50% of the sample at baseline would have undetectable viral load.

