#### Sample Size

Our sample size was selected to accommodate a range of 40–60% undetectable viral load at baseline, which we monitored in consultation with our Data Safety Monitoring Board (DSMB) to ensure enrolment of a sample with sufficient variability in viral load. Power analyses were generated using the two-group repeated proportions module in NCSS PASS 12 (76) to compute minimum detectable effect sizes at the proposed *N* and α = 0.05 and power = 0.80 for the primary analysis to evaluate Hypothesis 1 (TWH randomized to *Healthy Divas* will achieve or maintain higher odds of undetectable viral load than TWH assigned to a treatment as usual control condition). The study enrolled 278 participants evenly assigned to the intervention and control groups. Prior to starting implementation, we assumed 20% attrition, so that data from 228 participants would be available for analysis at all time points (i.e., 114 participants per group). We computed the minimum detectable odds ratio (*OR*), proportion difference (*pdiff*), and standardized proportion difference (*h*) for a time-averaged comparison, assuming four post-baseline measurements and assuming a range of virologic control base rates P_0_ and the within-subject correlation ρ was varied between.20 and.80 (see Table 5 for minimum detectable effect size estimates). Minimum detectable effect size estimates for our primary analyses fall between cutoffs of 0.20 and 0.50 for small and medium standardized effect sizes (77), respectively, suggesting that primary analyses have sufficient power to detect small to small-medium effects.

**Table 5 T5:** Within-subject correlations.

	**P**_**0**_ **= 0.30**			**P**_**0**_ **= 0.55**			**P**_**0**_ **= 0.80**		
**ρ**	* **OR** *	* **Pdiff** *	* **h** *	* **OR** *	* **Pdiff** *	* **h** *	* **OR** *	* **Pdiff** *	* **h** *
0.20	1.64	11.2%	0.235	1.61	11.6%	0.234	1.93	8.5%	0.235
0.30	1.71	12.3%	0.257	1.68	12.7%	0.257	2.07	9.2%	0.258
0.40	1.78	13.2%	0.275	1.75	13.6%	0.276	2.21	9.8%	0.277
0.50	1.84	14.1%	0.293	1.81	14.5%	0.294	2.35	10.4%	0.297
0.60	1.91	15.0%	0.311	1.88	15.3%	0.311	2.50	10.9%	0.314
0.70	1.97	15.8%	0.327	1.95	16.1%	0.328	2.65	11.4%	0.332
0.80	2.03	16.6%	0.344	2.01	16.8%	0.343	2.82	11.8%	0.347

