Therefore, we hypothesized that, following the intervention, the odds of undetectable viral load will be higher for intervention participants than for control participants (Hypothesis 1). Our primary interest was to estimate the marginal or population-average effect of intervention participation on each outcome rather than the effect for a hypothetical average subject. (93) Moreover, within-subject correlations among outcomes are considered nuisance parameters rather than quantities of interest to be modeled explicitly. Accordingly, generalized estimating equations (GEE) will be used to perform the proposed primary analysis, which is a planned time-averaged comparison of post-baseline measurements across the intervention and control groups to test primary Hypothesis 1. Alpha will be set at 0.05 for this planned comparison. Any additional *post-hoc* comparisons (e.g., paired comparisons of the control and intervention groups at each time point) will maintain a nominal alpha level of 0.05 through the use of simulation-based stepdown multiple comparison methods (94). Reflecting the binary nature of the virologic control outcome, a binomial distribution and logit link will be used for this analysis. Though GEE estimates are consistent even if the correlation structure is misspecified, GEE's statistical efficiency improves as the working correlation structure more closely approximates the actual correlation structure (95). Thus, working correlation structures suitable for the study's design will be considered (e.g., unstructured, AR (1), exchangeable, *M*-dependent) (96). The QIC statistic will be used to select the final working correlation structure (97). Robust Huber-White “sandwich” standard errors will be used to obtain correct inferences even if the chosen correlation structure remains slightly misspecified. GEE case deletion diagnostics (e.g., DFBetas, Cook's *D*) will be used to investigate whether influential cases are present; if such cases are found, results will be reported with and without influential cases included (98). As noted above, standard care quality (SCQ) will be included as a covariate in this analysis. In addition, randomization strata indicators will be included as covariates to obtain unbiased results (99). Additional covariates may be included if they improve QIC.

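### The claim that enrolling on poor engagement rather than detectable viremia gave more power and internal validity is unsupported; baseline virologic status should be a fixed covariate in the primary model.

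*Protocol article*

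**What the plan says.** Eligibility Criteria explains that the investigators considered enrolling only women with detectable viremia and chose indicators of poor engagement instead. It gives reasons of prevention, cost-effectiveness and external validity. It then adds a methodological one: "this decision allowed more statistical power, as the primary outcome could fluctuate in both directions for the two randomized groups", with greater internal validity as the consequence. It expects half the sample to be undetectable at baseline.

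Statistical Methods (Outcomes) defines the primary analysis as "a planned time-averaged comparison of post-baseline measurements across the intervention and control groups", by GEE with a logit link and a population-average target. Standard care quality and the randomisation strata are fixed covariates. Other covariates may enter if they improve QIC. Baseline viral load is not named there, and it is not among the stratification factors (site, age, race) in Sequence Generation.

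Hypothesis 1 (Objectives) is that women in the intervention arm "will achieve or maintain higher odds of undetectable viral load than TWH assigned to a treatment as usual control condition". Sample Size states that "Minimum detectable effect size estimates for our primary analyses fall between cutoffs of 0.20 and 0.50 for small and medium standardized effect sizes" and tabulates detectable effects by base rate and correlation. No calculation there compares the two eligibility options.

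**The concern.** The power of a between-arm comparison of post-baseline proportions depends on the control rate, the effect, the within-subject correlation and N. Whether individuals move up, down or both ways is not a further source of power. Internal validity rests on randomisation, concealment, follow-up and measurement, and is unaffected by the direction of change.

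Mixing women with low and high chances of suppression also has a cost that the text does not mention. Baseline status adds between-person variance, which raises the within-subject correlation, and every detectable effect in Table 5 grows with that correlation. The fixed covariates do not remove this variance, because baseline status reaches the model only if QIC happens to select it.

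Two things are at stake. The design is credited with an advantage that was never calculated, which could colour how a null result is read. And a strong predictor that was already measured is left to a data-driven choice.

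**Working it through.** **Inputs from the protocol (Sample Size).** "α = 0.05 and power = 0.80 for the primary analysis"; "data from 228 participants would be available for analysis at all time points (i.e., 114 participants per group"); "assuming four post-baseline measurements"; "the within-subject correlation ρ was varied between.20 and.80". A two-sided test is assumed, since it reproduces Table 5.

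**Step 1: reproduce Table 5.** Time-averaging four visits gives the variance factor D = (1 + 3ρ)/4 and an effective n of 114/D per arm. At ρ 0.20, D = 0.40 and n = 285. At ρ 0.80, D = 0.85 and n = 134. Solving a pooled-variance two-proportion test for 80% power gives:

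| P0 | ρ | Recomputed OR / pdiff | Table 5 |
|---|---|---|---|
| 0.30 | 0.20 | 1.64 / 11.2% | 1.64 / 11.2% |
| 0.30 | 0.80 | 2.03 / 16.6% | 2.03 / 16.6% |
| 0.80 | 0.20 | 1.93 / 8.5% | 1.93 / 8.5% |
| 0.80 | 0.80 | 2.82 / 11.8% | 2.82 / 11.8% |

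The middle column is labelled 0.55 but matches P0 = 0.50 (1.61 to 2.01). At a true 0.55 the detectable OR would be 1.62 to 2.05. The conclusion is the same either way.

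**Step 2: look for a gain in Table 5.** From P0 = 0.30 to the middle column:
- h is 0.235 against 0.234 at ρ 0.20, and 0.344 against 0.343 at ρ 0.80.
- The detectable OR falls by 0.02 to 0.03.
- The detectable difference rises by 0.2 to 0.4 points.

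That is no real gain, even before any rise in ρ.

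**Step 3: compare the eligibility options.** These assumptions are not in the protocol: control undetectable rates of 0.30 (detectable at baseline) and 0.80 (undetectable at baseline), a 50/50 mix, within-group ρ 0.5 (D = 0.625) and OR 2.0 in both groups. The OR moves 0.30 to 0.4615 and 0.80 to 0.8889. Power = Φ(difference/SE − 1.96).

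- *Detectable-only, 114 per arm.* SE = √[(0.2100 + 0.2485) × 0.625/114] = 0.0501. Then 0.1615/0.0501 = 3.22, so power is 90%.
- *Mixed, no baseline status.* The means are 0.550 and 0.6752, so the difference is 0.1252 and the marginal OR is 1.70. In the control arm the between-group variance is 0.25 × 0.5² = 0.0625 and the within-group variance is (0.21 + 0.16)/2 = 0.185. So ρ = (0.0625 + 0.5 × 0.185)/0.2475 = 0.63, and the variance of a person's four-visit mean is (0.2475 + 3 × 0.155)/4 = 0.1781. The intervention-arm figure is 0.1542. SE = √[(0.1781 + 0.1542)/114] = 0.0540. Then 0.1252/0.0540 = 2.32, so power is 64%.
- *Mixed, baseline status in the model, standardised difference.* Only within-group variance remains: SE = √[(0.185 + 0.1736) × 0.625/114] = 0.0443. Then 0.1252/0.0443 = 2.82, so power is 81%.
- *Detectable-only, 57 per arm.* SE = 0.0709 and 0.1615/0.0709 = 2.28, so power is 62%.

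A GEE simulation (logit link, robust standard errors, 600 runs) gave 89%, 63.5% and 81% for the first three.

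**Step 4: vary the effect.** Same formulas and control rates, ρ 0.5, power in %:

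| Effect | Detectable-only, 114/arm | Detectable-only, 57/arm | Mixed, no baseline | Mixed, with baseline |
|---|---|---|---|---|
| OR 2.0 in both groups | 90 | 62 | 64 | 81 |
| 12 points in both | 67 | 40 | 59 | 79 |
| 12 points detectable, 0 suppressed | 67 | 40 | 19 | 26 |
| 6 points detectable, 15 suppressed | 23 | 14 | 47 | 70 |

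For OR 2.0 the same four columns read 98, 81, 76, 94 at ρ 0.2 and 79, 50, 55, 68 at ρ 0.8. At equal N, the unadjusted mix breaks even when the risk difference in suppressed women is about 1.1 to 1.5 times that in detectable women.

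Testing a pooled within-group log odds ratio in the last column (variance [1/(p0q0) + 1/(p1q1)] × D/57 per group, inverse-variance weighted) gives 79, 76, 25 and 58. These also exceed the unadjusted figure in every row.

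**The case against.** The strongest reply is that the protocol's claim may be true in practice. A detectable-only criterion applied to the same recruits would yield about half the sample, and at 57 per arm the disadvantage of the unadjusted mix under OR 2.0 is gone (62% against 64%). The stated purpose is to prevent treatment failure. If benefit lies mainly in suppressed women, the mixed sample gains even at equal N (23% to 47%). If the detectable-only control rate were as low as 0.10, the detectable OR at ρ 0.2 would be 1.99, against 1.61 at 0.50, although the detectable difference would be smaller (8.1% against 11.6%). The QIC clause also permits baseline viral load to enter.

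All of this stands, and it rules out a stronger reading that a reader might infer: that the mixed sample simply lost power, by some 25 points. The documents do not show that. It needs assumed group rates, a common odds ratio, equal N and baseline status left out. Table 5 ties no base rate to an eligibility option.

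Nor does the point undermine the stated sample size. Table 5 does not rely on the sentence, and the mixed-sample correlation of 0.63 lies within its range. A pooled contrast is a legitimate test of Hypothesis 1, and supportive estimates by baseline status may sit in an analysis plan that is not shown.

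What the reply does not rescue is the reason given. A gain from a larger N, or from a larger effect in suppressed women, is not a gain from fluctuation in both directions, and none of it concerns internal validity.

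**Conclusion.** The statement on power and internal validity is unsupported: its mechanism does not apply to the primary analysis, and Table 5 shows no gain. The direction of any true power difference is undetermined by the documents. Under the assumptions of Step 3 at equal N it is 90% against 64%; it disappears at half the N and reverses when the effect is concentrated in suppressed women.

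One result held in all four effect patterns at ρ 0.5: including baseline virologic status raised mixed-sample power (64 to 81%, 59 to 79%, 19 to 26%, 47 to 70%). Those sizes rest on assumed control rates of 0.30 and 0.80 and a 50/50 mix. The correction to the text is minor, but the change to the model is worth making.

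**What to change.** - In Eligibility Criteria, delete the sentence on power and internal validity. Keep the prevention, cost-effectiveness and external-validity reasons, which stand by themselves. Do not replace it with an unconditional statement that power is lower.
- In Statistical Methods, name baseline virologic status as a fixed covariate in the primary GEE, beside standard care quality and the strata, instead of leaving it to QIC.
- Adjusting a logit model changes the odds ratio being estimated (2.0 within groups against 1.70 marginally in Step 3). Report the effect standardised over the baseline distribution, so that the population-average target is kept.
- Optionally, report the arm effect separately for women detectable and undetectable at baseline, as supportive estimates of achieving and maintaining control. They will be imprecise.

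The cost is one sentence, one model term and a standardisation step. Viral load was measured at baseline (Primary Outcome), so no new data are needed. The article says analyses were starting at submission, so the change should be dated before outcomes are compared by arm. If that point has passed, present the adjusted model as a labelled sensitivity analysis. Enrolment is complete, so eligibility itself is not in question.
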